Participants will receive acupuncture in private exam rooms in sessions that last about an hour. Brief interviews begin each subsequent session to review progress, prioritize symptoms, and identify any questions or concerns. After needle insertion, volunteers can expect to rest comfortably or nap. From 10 to 35 sterile, disposable needles will be inserted, with a technique characteristic of TCM known as “obtaining *de qi*,” an elicited response felt by both the patient and the acupuncturist. The needling sensation, adjusted for the comfort and safety of each patient, may be experienced as a pinch that rapidly subsides, or a sense of spreading pressure, dull ache, or warmth. Several types of needles, including from 32 to 38 gauge, and lengths from 15 mm to 50 mm, will be used on various parts of the body. Insertion depths vary by location, from subcutaneous to about 25 mm. Needles are retained 30-45 minutes. Choice of acupoints may vary during subsequent treatments to improve results.

A number of co-interventions will be used to supplement manual needling, usually 1 or 2 in each session, at the discretion of the acupuncturist. Electroacupuncture will be used for its efficacy in reducing pain and inflammation (59). Heat therapies will be used when appropriate, including heat lamp and moxibustion, a process in which a topical herbal product is heated on the needle or skin. Tui na, cupping and gua sha will be used, massage techniques in which rubbing, pressing, and scraping are applied to the body with the hands or with instruments. To prolong effects of treatment, tiny metallic balls, tacks or magnets may be applied to points after needling. The initial dose of acupuncture will be twice per week for 2 months, after which outcomes will be assessed and biological samples collected. For the following 4 months of treatment, the dose is reduced to once per week. The tapered dose of acupuncture is frequently used in clinical practice and has previously been used in research that demonstrated acupuncture efficacy for pain (9).

Volunteers in the control group will be offered 4 months of acupuncture once per week after the 2-month waiting period has elapsed. All volunteers will complete re-evaluation of outcomes instruments and biomarkers at the 6-month follow-up.

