Patient charts will include complete details of each volunteer’s assessment, diagnosis, and treatment. Interview guides in use at the New England School of Acupuncture’s clinic will be used in this study: Health History Questionnaire, TCM Intake, and TCM Follow-up (included in “Section B. Surveys, Questionnaires, and Other Data Collection Instruments”). As part of standard clinical practice, the acupuncturists’ notes will include assessment of response to treatment and any adverse events. Patients’ medical records will be stored in locked offices or filing cabinets, in compliance with regulations of privacy and security mandated by the Health Insurance Portability Act of 1996 (HIPAA).

Numerous studies have shown that acupuncture is safe when provided by professionally trained practitioners. Minor adverse effects of acupuncture may include needling pain, hematoma, and slight bleeding at the needle sites, as well as transient dizziness or drowsiness. (54). Serious adverse events are extremely rare**.** In a systematic review of 12 prospective studies scrutinizing over a million treatments, the very low risk of serious adverse event, mostly trauma from needle puncture or infection, was estimated at 0.05 per 10,000 treatments, a risk below that of many common medical treatments (95).

Several hypotheses of the mechanisms of acupuncture explain its likely effects on the symptoms of GWI. Acupuncture’s effects on peripheral nerves as well as the central and autonomic nervous systems play a role in its analgesic and anti-inflammatory effects. Although the etiology of GWI is unknown, researchers suspect that the symptoms reflect a spectrum of neurologic injury (16,86). Regulation of the endocrine system, mediated by the hypothalamus-pituitary-adrenal (HPA) axis (59), suggests a likely role for acupuncture in reducing stress. While GWI is not defined as a psychiatric disorder like posttraumatic stress disorder (PTSD), stress does play a role in the etiology of other multisymptom illnesses, such as irritable bowel syndrome, multiple chemical sensitivity and chronic headache (10). Stress reduction is likely to be of significant benefit, not only to those volunteers with emotional and cognitive disturbances, but to all the volunteers.

16. Description of Protocol Drugs or Devices.

No drugs are used in this study. The devices used are described in section “15. Study Procedures/Study Interventions” above.

17. Laboratory Evaluations.

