The Medical Monitor will review the treatment and measurement collection for safety. As required by the HRPO and/or our individual IRBs, the medical monitor will review all adverse events, whether or not they are serious or anticipated. He will review all unanticipated problems involving risk to volunteers, study staff, and others that are associated with the protocol and provide an unbiased written report within 10 days of the event to the HRPO and the individual IRBs. This report will include a description of the event, the outcome of the event, how it is (or is not) related to the study, and if it was anticipated. The report will also state if there is agreement between the medical monitor’s report and the details as provided by the PI. If either the PI or medical monitor believes that an event is possibly or definitely related to participation or if death is a result, the HRPO and the individual IRBs will promptly receive the report.

If a potential volunteer presents with a blood level at baseline that is out of range and it has clinical utility (for example c-reactive protein) we will inform them of this and suggest that they follow-up with their health care provider as recommended by the medical monitor. As directed by the IRB, we will inform the volunteer that we are happy to send these results to his/her primary care provider with their permission. If they want to follow-up with their doctor we will collect from them their health care provider information and we will send the provider the results.

Study Organization and Management Plan

Please find below **Figure 6:Organizational Chart** which gives an overview of the responsibilities and regular communication between different roles on the study team. The PI will oversee all operations and communicate with all coordinators and consultants. The Data analysis coordinator will work directly with the statistical consultant. The acupuncture coordinator, under the direction of the PI and the Senior acupuncture coordinator will work together to organize the treatment training and protocols. The Project Coordinator will communicate with all levels of the team and directly supervises the Research Assistants. The Biomarker Coordinator mainly communicates with the PI, but her input is welcome at team meetings. The medical monitor interfaces with the PI and Data analysis coordinator to assure volunteer safety.

Figure 7 below is a timeline of study activities from start up to final manuscript preparation.

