All serious protocol deviations that may have an effect on the safety, or rights of a volunteer or the integrity of the study, will be reported to the HRPO within 10 days of the event. All protocol deviations, regardless of their severity or relatedness to the study, will be reported to the participating IRBs within 10 days of the event. The study coordinator will work with the PI to complete and submit the necessary paperwork.

26. Reporting of Serious Adverse Events and Unanticipated Problems

An adverse event is any health change (or side-effect) that happens to a volunteer while he/she is participating in the study. The PI has the primary responsibility of reporting adverse events and will work with the study coordinator to submit all paperwork. All adverse events, regardless of severity, will be reported to our participating IRBs using their standard forms. These forms need to be submitted within 10 days for non-serious events. Volunteers who report a serious adverse event will be escorted to the nearest emergency room if the event happens during a study treatment. If the event happens while the volunteer is enrolled in the study, but not actively engaging in study activities, he/she will be directed to seek medical care either through his/her regular provider or through the use of a local emergency room.

This funding mechanism requires the procedures as outlined in the application on page 41, as stated in the cited text below.

“Unanticipated problems involving risk to volunteers or others, serious adverse events related to participation in the study, and all volunteer deaths related to participation in the study should be promptly reported by [contact]), by email ([contact]), or by [contact]) to the US Army Medical Research and Materiel Command’s Office of Research Protections, Human Research Protections Office. A complete written report should follow the initial notification. In addition to the methods above, the complete report can be sent to the US Army Medical Research and Materiel Command, ATTN: MCMR-ZB-P, [name].”

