**B. Surveys, Questionnaires, and Other Data Collection Instruments**

**(Copies of all scales are below.)**

Baseline Measurements

Screening:

- Primary Care Evaluation of Mental Disorder (Prime MD) (81)

Data Collection:

- - The Sf-36 (53)
- Multidimensional Assessment of Fatigue (85)
- The Profile of Mood States (62)
- Pittsburg Sleep Quality Index (34)
- Measure Your Medical Outcomes Profile (40)
- Beck Anxiety Inventory (63)
- McGill Pain Scale (55)
- Carroll Depression Scale (14)
- Social support, Social Networks, and Stress (56-7)
- Medication use and Expectations for Treatment
- Blood draw to examine levels of selected markers of inflammation, stress, and immune function.

Endpoint Measurements:

- - The Sf-36 (53)
- Multidimensional Assessment of Fatigue (85)
- The Profile of Mood States (62)
- Pittsburg Sleep Quality Index (34)
- Measure Your Medical Outcomes Profile (40)
- Beck Anxiety Inventory (63)
- McGill Pain Scale (55)
- Carroll Depression Scale (14)
- Social support, Social Networks, and Stress (56-7)
- Medication use and Expectations for Treatment
- Blood draw to examine levels of selected markers of inflammation, stress, and immune function.

Follow-up Measurements:

- - The Sf-36 (53)
- Multidimensional Assessment of Fatigue (85)
- The Profile of Mood States (62)
- Pittsburg Sleep Quality Index (34)
- Measure Your Medical Outcomes Profile (40)
- Beck Anxiety Inventory (63)
- McGill Pain Scale (55)
- Carroll Depression Scale (14)
- Social support, Social Networks, and Stress (56-7)
- Medication use and Expectations for Treatment
- Blood draw to examine levels of selected markers of inflammation, stress, and immune function.
- Debriefing and brief interview about study experience

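### In months 0-2 the only routine adverse-event recording described is in the acupuncturists' session notes, so event capture is unequal between the arms

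*Protocol*

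**What the plan says.** **Definition and duty (Protocol section 26).** The definition is broad and not limited by arm: "An adverse event is any health change (or side-effect) that happens to a volunteer while he/she is participating in the study". So is the reporting duty: "All adverse events, regardless of severity, will be reported to our participating IRBs using their standard forms". Responsibility for reporting lies with the PI and the study coordinator, not with the acupuncturists.

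**Review.** The medical monitor text before section 23 says that "the medical monitor will review all adverse events, whether or not they are serious or anticipated".

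**Recording (section 15).** The acupuncturists' "notes will include assessment of response to treatment and any adverse events". The sentence presents this as part of ordinary clinical practice and does not call it the sole source.

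**Contact with acupuncturists (section 15).** The acupuncture arm is treated twice a week for the first 2 months, and each session after the first opens with a short interview on progress and concerns. For the other arm: "Volunteers in the control group will be offered 4 months of acupuncture once per week after the 2-month waiting period has elapsed".

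**Common assessments (section 18 and Section B).** Both arms complete the same instruments at baseline, at the 2-month endpoint and at the 6-month follow-up. The lists go down to medication use and the blood draw. None names an adverse-event form or question. The nearest item is at follow-up only: "Debriefing and brief interview about study experience".

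**Analysis (section 18).** The stated between-group tests concern the SF-36 and the secondary outcomes. No between-arm test of adverse events is stated.

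**The concern.** Section 26 counts any health change as an adverse event. Gulf War Illness brings many fluctuating complaints, so background events will be common in both arms, and how many are recorded depends on how often someone asks. As described, one arm is seen twice a week by a practitioner who notes events, and the other has no described occasion for this until the comparison period is over.

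The wait list is the concurrent control. It could help separate effects of acupuncture from the natural course of the illness; the protocol's own risk section cites transient aggravation of symptoms in 1.0-2.8%. It can do so for adverse events only if both arms are asked in the same way. Unequal asking is a fault in data collection, and no later analysis can restore events that were never recorded.

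Two smaller consequences follow. An acupuncture volunteer who stops attending leaves the one routine source described. And section 26 sets a 10-day limit for submitting non-serious events to the IRBs, while no described procedure tells the study promptly about events in waiting volunteers.

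**Working it through.** The plan states no figure on this point, so there is none to reproduce. The check is a count of recording occasions, followed by an illustration of the possible bias.

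**1. Recording occasions before the 2-month comparison**

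- Acupuncture arm (section 15): 2 sessions per week x 8 weeks = 16. Taking 2 calendar months as 2 x 365.25 / 12 / 7 = 8.7 weeks gives 2 x 8.7 = about 17.
- Wait-list arm (section 15): 0, because acupuncture is offered only after the waiting period.
- Adverse-event items named at the common 2-month assessment (Section B): 0 in both arms.

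Section 18 says the wait-list group receives study attention during these 2 months but does not say what that consists of, so it cannot be counted as a recording occasion.

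**2. What the other adverse-event provisions add**

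- Section 26 settles what counts as an event and who reports it. The monitor text and section 20 settle who reviews it. All of these apply to both arms.
- Section 26 also foresees a serious event away from study activities: "If the event happens while the volunteer is enrolled in the study, but not actively engaging in study activities". That covers the waiting period, but the rest of the sentence says where the volunteer seeks care, not how the study learns of the event.
- Section 24 asks all volunteers to an exit interview when participation ends. It is about study experience and is not described as an adverse-event inquiry.

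Together these provide for events once they are known. For waiting volunteers, the way of becoming known appears to be spontaneous report.

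**3. Possible size of the bias (assumptions, not protocol figures)**

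Let p be the true 2-month risk of at least one event, equal in both arms. Let capture be complete in the acupuncture arm and a fraction c in the wait-list arm. The spurious excess is

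excess = p - p x c = p x (1 - c).

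| p | c | Recorded, acupuncture (of 60) | Recorded, wait list (of 60) | Spurious excess |
|---|---|---|---|---|
| 10% | 75% | 6 | 4.5 | 2.5 points |
| 10% | 25% | 6 | 1.5 | 7.5 points |
| 20% | 50% | 12 | 6 | 10 points |
| 30% | 75% | 18 | 13.5 | 7.5 points |
| 30% | 25% | 18 | 4.5 | 22.5 points |

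The 60 per arm is the analysed number in section 12. The excess is zero if capture is equal (c = 1). It reaches the full 10-30 points only if nothing is captured on the wait list (c = 0), which the text does not establish.

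**The case against.** The strongest reply is that a reader might infer that wait-list volunteers have no adverse-event capture at all and that any safety contrast is one-sided by construction. The documents do not support that.

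- Section 15 does not make the session notes the sole record, and the definition, reporting duty and monitor review cover every volunteer from enrolment. This stands: spontaneous report is open to both arms.
- The available text is incomplete. Most of the study personnel section is absent and could assign adverse-event duties to other staff. Section B announces copies of the scales, which are not shown, and its list omits clinic interview forms that section 15 says it contains. This stands as a limit: one can say that no other routine route is described, not that none exists.
- No between-arm safety test is planned, and finding a safe treatment is mentioned as a potential of the study, not as an objective in section 7. This stands: no prespecified test is damaged.
- Symptom worsening is measured equally in both arms through the fatigue, mood, pain, sleep, anxiety and depression scales. This stands for net symptom change between assessments. It does not cover new health problems, or events that came and went before the 2-month visit.
- At 1.0-2.8%, transient aggravation would affect about 0.7 to 1.9 of 67 treated volunteers (67 x 0.010; 67 x 0.028), too few to separate from natural course even with perfect capture. This is fair for that one event type. It does not justify unequal recording of the rest.

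What the reply leaves untouched is the imbalance in active inquiry: about 16 occasions against none, with no common question named.

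**Conclusion.** The point holds as one about unequal ascertainment. On the available text, routine adverse-event recording in the randomised period is tied to treatment sessions that only one arm attends, and wait-list events appear to rest on spontaneous report. A comparison of event counts for months 0-2 would be biased towards more events on acupuncture.

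The direction follows from the design; the size does not, because the protocol gives neither an event rate nor a capture rate. The range of 2.5 to 22.5 percentage points rests on three assumptions: a 10-30% true risk equal in both arms, full capture in the acupuncture arm, and 25-75% capture in the wait-list arm. Figures built on zero wait-list events would be an upper bound and should not be cited as expected.

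The harm is to any safety statement drawn from the randomised period, not to the primary analysis. Confidence is limited by the missing personnel text and forms. The change is still worth making because it is cheap and the gap cannot be closed after data collection.

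**What to change.** Add one identical adverse-event question to the 2-month and 6-month batteries in Section B: any new or worsened health problem since the last assessment, with its date, seriousness and outcome. Research assistants should put it to every volunteer in both arms, including those who have stopped acupuncture.

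State that any between-arm safety statement for months 0-2 rests on this item only. Report events from session notes separately, as a description of experience under acupuncture. If another capture route for waiting volunteers already exists in text or forms not available here, name it in section 26 and align it across arms.

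The cost is a protocol amendment, one short form at two visits that already take place, a few minutes per visit and more events to report to the IRBs. Two limits remain. A question asked at 2 months does not by itself meet the 10-day reporting limit for earlier events. And because the trial is unblinded, equal asking does not guarantee equal willingness to report.

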**GWI Registry**

**“Opt Out” letter**

**Opted Out (refused)**

**Advertisements**

**Initial Screening**

**(Telephone)**

**INELIGIBLE**

**Medical Screening**

**INELIGIBLE**

**Eligible Volunteers**

**Treatment**

**Waitlist**

**Follow-up**

**Follow-up**

**`**

12. Sample Size Justification.

Our study is designed to give us adequate power to detect clinically meaningful differences between treatment groups. Previous acupuncture research using our main outcome, the SF-36, in pain conditions (41,52) show a consistent standard deviation of 20 points in the Physical Component Summary score of the SF-36 for both baseline values and change scores. Sixty individuals per group (total n=120) would offer us a power of 80% to detect the difference between groups of 7 points. Using Cohen’s d estimation of effect size (20):

[figure not shown]

A sample size of 60 will allow us to see a moderate effect. In further support of our main outcome a 7 unit improvement has been shown to be clinically relevant (97,55,78).

Although we do not expect attrition to be large, we expect a dropout rate of no more than 10% by the 8 week endpoint. This trial is longitudinal which could increase drop-out rate. Still a veteran’s population will be less mobile and may have fewer other options for care; both of these factors should increase adherence. We will thus oversample to a target sample size of 67 volunteers per group to assure that our power to detect effects is maintained. The resulting overall sample will be 134 (one treatment group and one wait list group).

13. Description of Informed Consent Process.

The informed consent process will occur in two stages. Verbal informed consent will be administered prior to the initial telephone screening, and written informed consent will be administered in person, at the start of the screening visit.

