We will be collecting a small blood sample at the three data collection points and a research assistants will immediately transport the blood on ice to [name] lab. We are collecting and analyzing these data to better understand the mechanisms of GWI and changes associated with acupuncture. We are focusing on inflammatory changes, immune function, and markers of stress. For example we are interested in the relationship between acupuncture treatment, reported stress, and immune function. Multiple studies have looked at this relationship. For example recent research suggests that acupuncture modulates serum concentrations of inflammatory cytokines; for example, acupuncture reduces cytokine levels in a rat model of inflammation (79) and in asthmatic patients receiving a gentle form of Korean acupuncture (42). It is not surprising then that we have found in our IBS data set that individuals with greater decreases in reported stress had associated immunological changes as measured by a reduction in the percentage of circulating activated T-lymphocytes (CD69+). Toward the exploration of immunophenotyping, blood will continue to be collected with patient consent at the initial screen, at midpoint and at follow up. Mononuclear cells will be stained with a panel of antibodies (DAKO Cytomation) against markers of leukocyte differentiation and activation and analyzed using the Cell Quest program as described above. In parallel, serum cytokine levels (IFNγ, IL-2, IL-2R, IL-7, IL-4) will be measured by ELISA (R&D systems) and serum cortisol levels, as a surrogate biological marker for stress, by a radioimmunoassay. The evaluations at 3 different time points will enable us to identify immunological markers that are predictive of clinical response to acupuncture treatment (initial point) or are associated with it (endpoint). Initial analysis will be performed using ANOVA factorial with Bonferroni correction for multiple comparisons and ANOVA repeated measures for the overtime changes in immune status. If the results of this analysis warrant, a feature selection multivariate analysis will be performed that takes into account higher order interactions among the variables.

18. Data Analysis.

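### If run in its classical form, the repeated-measures ANOVA of the three blood draws drops every volunteer without a 6-month draw, including that volunteer's baseline-to-2-month data; a mixed model on all available draws avoids this

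*Protocol*

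**What the plan says.** Section 17 of the protocol names two initial marker analyses in one sentence. The first reads "Initial analysis will be performed using ANOVA factorial with Bonferroni correction for multiple comparisons". The second is "ANOVA repeated measures for the overtime changes in immune status".

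The draws are described twice in that section: "We will be collecting a small blood sample at the three data collection points" and "blood will continue to be collected with patient consent at the initial screen, at midpoint and at follow up". Section 15 (Study Procedures/Study Interventions) fixes the timing. Acupuncture is given "twice per week for 2 months, after which outcomes will be assessed and biological samples collected", and "All volunteers will complete re-evaluation of outcomes instruments and biomarkers at the 6-month follow-up". The three draws are therefore at baseline, 2 months and 6 months.

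On attrition, section 12 (Sample Size Justification) says "we expect a dropout rate of no more than 10% by the 8 week endpoint" and adds "This trial is longitudinal which could increase drop-out rate". It then argues that veterans are less mobile and may have fewer other care options, which should help adherence. It gives no figure for loss between months 2 and 6.

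Section 18 (Data Analysis) plans Student's t-tests between groups for secondary outcomes. It also says that the arms are not directly comparable at 6 months, because wait-list members will by then have had acupuncture.

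The protocol does not say whether the repeated-measures ANOVA is classical or a mixed model, or which analysis supplies the 2-month between-arm marker comparison.

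**The concern.** A classical repeated-measures ANOVA works on complete sets of measurements. With three draws, a volunteer who gave blood at baseline and at 2 months but not at 6 months contributes nothing, even to the baseline-to-2-month part of the model.

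That part matters most. By the protocol's own account the arms cannot be compared directly at 6 months, so month 2 is the only point at which a marker difference between arms is a randomised comparison. Restricting it to people who stayed until month 6 does two things:

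- It discards samples already collected and assayed.
- It makes entry into the comparison depend on an event after randomisation. Between months 2 and 6 one arm continues a course already two months old while the other is just being offered treatment. Reasons for leaving could therefore differ by arm.

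**Working it through.** **Inputs from the protocol.** 60 evaluable and 67 enrolled per group; at most 10% lost by week 8 (section 12). Three draws (sections 15 and 17).

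**Assumed, because the protocol gives no figure.** A further 5-15% of enrolled volunteers lost between months 2 and 6. For the bias illustration, a correlation of 0.3-0.5 between marker change and clinical benefit.

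**Step 1: the plan's own figure.** 60 / (1 - 0.10) = 66.7, rounded up to 67 per group. This reproduces.

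**Step 2: usable data per arm.**
- Baseline and 2-month pair: 67 × 0.90 = 60.3, about 60.
- All three draws, further 5% lost: 67 × 0.85 = 57.0, about 57.
- All three draws, further 15% lost: 67 × 0.75 = 50.3, about 50.
- Pairs discarded: 60 - 57 = 3, up to 60 - 50 = 10.

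**Step 3: precision.** The standard error varies as 1/√n.
- 5% further loss: √(0.90/0.85) = 1.03.
- 15% further loss: √(0.90/0.75) = 1.10.

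The standard error of the 2-month contrast within that model thus rises by about 3-10%. As a cross-check, late loss can be expressed as a share x of those who reached month 2, so that the ratio is √(1/(1 - x)). For x = 5%, 10% and 20% the rise is 2.6%, 5.4% and 11.8%. For an illustrative 0.5 SD effect at a two-sided 0.05 level, before any Bonferroni correction, power falls from 78% to 76%, 74% and 69%.

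**Step 4: when bias arises.** Large simulated arms (200,000 each) had a true 2-month difference of 0.50 SD of change. Late loss was 5%, 10% or 20% of month-2 attenders.

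| Late loss | Difference among three-draw completers |
|---|---|
| Random | about 0.50 throughout |
| Related to response, equally in both arms | about 0.50 throughout |
| Related to response, acupuncture arm only; random in the wait-list | 0.55, 0.59, 0.67 |

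In the last two rows the chance of leaving depended directly on the marker change (logistic, one unit of log-odds per SD). That is a strong link.

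**Step 5: size of bias with a weaker link and no true effect.** Suppose leaving depends on clinical benefit, and benefit correlates 0.3-0.5 with marker change. The shift in the driver of dropout is then multiplied by that correlation.
- Moderate selection: Step 4 gives shifts of 0.59 - 0.50 = 0.09 at 10% loss and 0.67 - 0.50 = 0.17 at 20%. Then 0.09 × 0.3 = 0.03 and 0.17 × 0.5 = 0.09 SD.
- Extreme case, where exactly the least-improved leave: the mean of a standard normal with its lowest fraction p removed is φ(z_p)/(1 - p). For p = 10% this is 0.1755/0.90 = 0.195; for p = 20% it is 0.280/0.80 = 0.350. Then 0.195 × 0.3 = 0.059 and 0.350 × 0.5 = 0.175 SD.

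The 20% case lies above the range in Step 2, where 15% of enrolled is 0.15/0.90 = 16.7% of month-2 attenders.

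**The case against.** The strongest objection is that the protocol never says volunteers with a missing draw are excluded. Complete-case deletion is inferred from the name of the method, and some analysts use the same name for a mixed model. How to handle missing exploratory samples is also something a statistical analysis plan commonly settles. This stands as a limit on the claim, which is why it is conditional on the classical form. It does not remove the point: section 17 names a method whose ordinary form discards partial data, and a better one is readily available.

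A reader might infer that late leavers are removed from the 2-month marker comparison altogether. The documents do not support that. The factorial ANOVA in the same sentence could use everyone with a 2-month sample. So could the t-tests that section 18 plans for secondary outcomes, if markers count among them. The loss is established only for the repeated-measures model.

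A reader might also infer that the comparison will be biased. That does not follow either. Step 4 shows essentially no bias when late loss is random, or when it is related to response equally in both arms.

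Finally, the markers are exploratory, every late-loss rate used here is assumed, and section 12 gives reasons to expect good adherence as well as reasons to expect dropout. All of this stands, and it keeps the point minor.

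**Conclusion.** The point holds in conditional form. In its classical form, the planned repeated-measures ANOVA would exclude volunteers who have 2-month blood but no 6-month blood from its baseline-to-2-month and arm-by-time information. If a further 5-15% of enrolled volunteers are lost after month 2, the cost within that model is about 3-10 pairs per arm and a standard error 3-10% larger.

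Bias requires late loss that is both related to response and different between arms. With no true effect, a correlation of 0.3-0.5, and 10-20% of month-2 attenders leaving selectively from the acupuncture arm alone, the false contrast is about 0.03-0.09 SD under moderate selection. It reaches 0.059-0.175 SD in the extreme case. These are illustrations, not predictions.

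The primary SF-36 analysis is not touched. The importance is low and the remedy is cheap.

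**What to change.** In section 17, replace the repeated-measures ANOVA with a linear mixed model for repeated measures fitted to all available draws, with arm, visit and arm-by-visit terms and an unstructured covariance. Take the 2-month arm contrast from that model, so that everyone with a 2-month sample contributes, and keep the planned Bonferroni correction.

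The cost is one sentence and slightly more modelling work. The model assumes data are missing at random, which is weaker than what a complete-case analysis needs. For volunteers lost only after month 2, the 2-month value is already in hand and enters the contrast directly, so the assumption bears mainly on earlier loss and on the 6-month estimates.
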